### Plans to give access to the full protocol, participant level-data, and statistical code {31c}

The protocol of the study is publicly available on ClinicalTrials.gov identifier (NCT06405360). After the completion of the study, the de-identified data will be deposited into the Data Repository of the University of Florida and the USAID data repository, where it can be publicly accessed. The dataset in the USAID repository will be findable and identifiable through a study DOI.

## Oversight and monitoring

### Composition of the coordinating center and trial steering committee {5d}

The study is a single-site RCT in Rwanda. A trial manager at World Vision-Rwanda will be responsible for the day-to-day field activities and will be responsible for managing the field team, including a project facilitator, data management officer, nurse sonographers, food aid distributors, and egg preparation staff. To enhance collaboration and ensure project effectiveness, regular weekly team meetings will be held among the study team at the University of Florida, University of Rwanda, World Vision US, and the World Vision Rwanda field team. Protocols for data collection and sharing will be shared to ensure transparency and accessibility. A quarterly update will be communicated to partners in the GoR, including the National Child Development Agency, the Rwandan Biomedical Center, the Rwanda Agricultural Board, and other key stakeholders.

### Composition of the data monitoring committee and its role and reporting structure {21a}

The data monitoring committee members will include the PI, the PI at World Vision US, a data management consultant at the REDCap office within UF’s Clinical Translational Science Institute, a data manager with the field team, and a postdoc at UF. The committee will meet at least every 3 months. The committee will ensure the protection of the interests of study participants and ensure the integrity of the study conduct and results.

### Data monitoring: interim analysis {21b}

An interim analysis will be conducted after data are available for approximately 100 births and will be focused on secondary outcomes. No interim analysis will be conducted on the primary outcome (birth length) of the study. This analysis will primarily focus on feasibility, safety, and adherence to the intervention, rather than formal hypothesis testing. The principal investigator and study team will review these findings.

### Adverse event (AE) reporting and harms {22}

Any adverse event, including a clinically significant abnormal laboratory finding, symptom, or disease temporally associated with the study, will be monitored and reported in detail in the participant’s records. AEs will be coded following MedDRA terminology to ensure consistent classification, analysis, and reporting. In trial publications, we plan to report all serious adverse events (SAEs) as well as any AEs deemed related to the intervention. The PI will evaluate and follow up with all AEs and inform regulatory bodies as appropriate (RNEC and UF-IRB) of measures that will be executed accordingly.

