## Interventions

### Explanation for the choice of comparators {6b}

The intervention group will receive a daily supplement of two eggs (with consumption directly observed) from enrollment in the first trimester through childbirth. Both the intervention and control groups will receive standard information, education, and communication (IEC) about healthy diets and appropriate care during pregnancy. Participants will not be restricted from adding eggs or any other food to their diet.

All enrolled participants will receive the Government of Rwanda’s (GoR) up-to-date standard care for pregnant women, a mobile phone, health insurance (if not already covered), and modest compensation for traveling to a community health worker’s (CHW) home daily for study engagement. Additionally, any pregnant woman not already receiving the government-provided fortified corn-soy blend (CSB++ or *Shisha Kibondo*) will receive an equivalent amount (6 kg) from the study.

In order to uphold ethical considerations and account for potential spillover effects of the intervention, the study design does not include a true control group. The control group will receive the same level of care, information, education, and communication (IEC), and equal amount of CSB+; only egg supplementation will be different between the two groups. This design allows for a clear comparison of the effects of egg supplementation on pregnancy and child growth outcomes, beyond the benefits of a typical diet that includes CSB+ .

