### Intervention description {11a}

All women enrolled in the study will be asked to visit a designated village-based consumption site (CHW’s home) daily. Sites must be within a 20-min walk from women’s homes. When a CHW house is not within a 20-min walk, additional sites (such as the home of a World Vision volunteer) will be identified close to the participant’s house. Study staff will prepare and transport hard-boiled eggs daily to CHWs’ houses (or designated consumption site), where CHWs will distribute eggs to the women in the intervention group every day. Study staff will observe and record consumption (no consumption, partial, or complete). The study staff will also ask about 24-h recall of quantity and consistency of CSB+ consumption and any adverse reaction or allergy to eating eggs. Women in the treatment arm and the control arm will both receive IEC communication. All women (treatment and control) will be compensated for their daily travel to the CHW’s house. The daily compensation of 500 RWF per day will be paid on a weekly basis if women attend at least 6 days in a week. However, in cases of excused absence, they will receive daily compensation for those days.

Participants in both the intervention and control groups will receive guidance to maintain their usual diets outside of the study intervention. No dietary restrictions will be imposed.

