### Relevant concomitant care permitted or prohibited during the trial {11d}

Participants will not be restricted from adding eggs or any other food to their diet.

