### Procedure of unblinding if needed? {17b}

Staff conducting data quality checks and staff doing the intervention delivery will only be unblinded to the allocated intervention. All other study staff will remain blinded.

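### Non-serious adverse events are published only if judged related to the eggs, so that part of the harms report gives no fair comparison between arms

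*Protocol article*

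**What the plan says.** The section Adverse event (AE) reporting and harms {22} sets a wide net for collection: "Any adverse event, including a clinically significant abnormal laboratory finding, symptom, or disease temporally associated with the study, will be monitored". Events go into the participant's records and are coded with MedDRA. Publication is narrower: "we plan to report all serious adverse events (SAEs) as well as any AEs deemed related to the intervention". Serious events are thus published in full. A non-serious event is published only if someone attributes it to the intervention, and the same section states that "The PI will evaluate and follow up with all AEs".

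The section Explanation for the choice of comparators {6b} says that "only egg supplementation will be different between the two groups". Under Intervention description {11a}, "All women enrolled in the study will be asked to visit a designated village-based consumption site (CHW’s home) daily", so staff see both arms equally often. The harm item stated for that daily contact is "any adverse reaction or allergy to eating eggs". Concomitant care {11d} adds: "Participants will not be restricted from adding eggs or any other food to their diet".

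**The concern.** A randomised trial with a concurrent control group, seen as often as the treated group, can separate events caused by the supplement from events that occur in pregnancy anyway. Nausea, vomiting, rash and abdominal symptoms need that comparison, because no single case can be attributed reliably. The publication rule puts a case-by-case judgement in place of the comparison, and only one arm can readily meet the condition.

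The error can run either way. Ordinary complaints attributed to eggs would look like an excess over a nearly empty control column. A true excess of complaints that nobody attributes to eggs would be missing from the published non-serious events. The Discussion says the results will inform nutrition policy, so the tolerability of daily eggs is something readers will look for.

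**Working it through.** **Step 1. Set the passages side by side.**
- Recorded: any adverse event, in any participant (section {22}).
- Published: all serious events, plus non-serious events judged related (section {22}).
- Planned difference between arms: eggs only (section {6b}).
- Stated daily harm question: reactions to eating eggs (section {11a}). The text does not say that only the egg arm is asked. Even if both arms are, the question means little to a woman given no study eggs, apart from eggs she eats by choice (section {11d}).

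It follows that non-serious events pass into print freely from the egg arm and hardly at all from the control arm, and that daily prompting is unequal in content.

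**Step 2. Check the denominator.** The plan gives no harms figure. Its one design figure is 478 women per arm (Sample size {14}). With a difference of 0.18, an assumed SD of 1.0 (none is stated), one-sided 5% and 80% power:

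n = 2 × (1.645 + 0.842)² / 0.18² ≈ 382 per arm; 382 / 0.80 = 477.5, rounded up to 478.

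The stated figure reproduces and is used below.

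**Step 3. Illustrate the filter with no egg effect.** Let p be the share of women with a non-serious complaint, the same in both arms, and r the share of egg-arm cases judged related. Both are assumptions. The published egg-arm count is 478 × p × r; the control count is taken as 0. The p-values are from Fisher's exact test.

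| p | r | Egg arm v control | Fisher p |
|---|---|---|---|
| 5% | 10% | 2 v 0 | 0.50 |
| 5% | 30% | 7 v 0 | 0.015 |
| 10% | 10% | 5 v 0 | 0.06 |
| 10% | 30% | 14 v 0 | 0.0001 |
| 20% | 10% | 10 v 0 | 0.002 |
| 20% | 50% | 48 v 0 | <0.0001 |

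At p = 20%, 478 × 0.20 = 95.6 women per arm have the complaint; × 0.25 gives 23.9, or 24 v 0. The true difference in risk is zero in every row. What moves the count is r, the readiness to attribute.

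**Step 4. What the unfiltered table would offer.** With 478 per arm, all contributing, a two-sided 5% test has this power:
- control risk 5%: 84% for a doubling, 36% for a 1.5-fold risk;
- control risk 10%: 99% for a doubling, 65% for a 1.5-fold risk.

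For common complaints the comparison that the rule discards would be informative.

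**The case against.** The strongest reply is that the trial's safety information does not rest on the non-serious table. All serious events are published from both arms with no relatedness condition. Table 1 lists the lipid panel, blood pressure with hypertension, preterm birth, low birthweight and small-for-gestational-age as outcomes. Section {18a} asks all women about medical conditions since the last visit at the two later antenatal visits. Section {22} records and codes every event, so the data will exist. All of this stands, and it limits the point to non-serious events.

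Three stronger readings are tempting and are not supported.
- A reader might infer that the trial cannot show whether eggs cause harm, or that a rise in cholesterol or glucose would go unseen. The serious events and the outcomes just listed contradict the first. For the second, lipids are an outcome in Table 1, and section {33} has lipids and glucose measured in women at each trimester visit and at both postpartum visits.
- A reader might infer that control events are zero by definition. Control women may eat eggs, and Table 2 lists health messages to both arms under the intervention heading, so a few could be judged related. Close to zero is a fair expectation; exactly zero is not established.
- A reader might infer that a blinded principal investigator has to judge relatedness without knowing the arm. That rests on one general sentence, "All other study staff will remain blinded". The list of blinded roles in section {17a} does not name the principal investigator, so the documents do not settle the matter.

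It is also fair to say that the counts above restate assumed rates, and that the plan promises to report related events, not to test them between arms. But a list by arm will be read as a comparison, and no other between-arm comparison of non-serious events is stated.

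**Conclusion.** The point holds for non-serious adverse events. Under the publication rule and the stated daily question, control-arm non-serious events will be almost entirely left out, and what is published cannot tell a higher risk from a greater readiness to attribute. The direction follows from the text alone. The size cannot be fixed, because the documents give no event rates or attribution shares; over the assumed ranges the spurious contrast runs from 2 v 0 to 48 v 0.

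This is a fault in reporting and in daily prompting, not a loss of all safety data. It should be corrected because the correction is cheap and the control data will already have been recorded. It does not touch the primary analysis.

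**What to change.** **Section {22}.** Replace the publication rule with a statement that all recorded adverse events, serious and non-serious, will be tabulated by randomised arm whatever their judged relatedness, and that relatedness will appear only as an additional column. This also covers women already enrolled, since their events are recorded under the present text.

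**Section {11a}.** Add one short general symptom question, worded identically and asked of both arms at the daily visit. Keep the egg-reaction question as an extra item, asked after the general one and reported separately, so that it does not bring back unequal prompting. Start the new form in both arms on the same date. The Trial status section says new enrolment is paused, which is a convenient time to amend.

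**Cost.** A protocol amendment with ethics approval, an edit to the REDCap form, a longer adverse event table and a slightly longer daily form. No new visits are needed, because both arms already attend daily. Answers to the general question will be missing for the period before the change, and the report should say so.

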### Frequency and plans for auditing trial conduct {23}

The monitoring and evaluation team from UF will have monitoring visits at least biannually. The monitoring team will review the study conduct and compliance with the study protocol, good clinical practice, standard operating procedures, and applicable regulatory requirements.

### Plans for communicating important protocol amendments to relevant parties (e.g., trial participants and ethical committees) {25}

Any amendments to the study protocol deemed necessary will be discussed between the PI and Co-PIs. No changes to the protocol will be implemented without prior review and documented approval from the RNEC and UF-IRB, except when required to eliminate an immediate risk to study participants.

### Dissemination plans {31a}

The study findings will be disseminated through peer-reviewed scientific journal publications and conference presentations and will be available on the project website. Results will be communicated to the participants, Ministry of Health of Rwanda, field staff, and other relevant national and international stakeholders. Results will be shared in accessible formats, such as community meetings led by local health workers and summary brochures provided in the local language.

## Discussion

This paper describes the protocol for *Deux Oeufs*, an individually randomized two-arm trial in *Nyagatare* District, Rwanda, in which pregnant women in the intervention group will consume two eggs per day under direct observation from the first trimester through childbirth. The *Deux Oeufs* study will provide evidence of the impact of egg supplementation during pregnancy on a child’s physical and cognitive development. Formative research was conducted in Rwanda before finalizing the design of the trial. Carrying out the formative research allowed the study team to identify strengths and potential pitfalls, as well as identify appropriate study sites and further engage partners and stakeholders. The findings from the formative research and details of how they informed the study protocol presented here are currently under preparation. The main strength of this protocol is that it will be the first RCT, to our knowledge, to study the effect of egg consumption in pregnant women on the nutritional outcomes of the child. The Rwandan government has identified stunting as one of the four national priorities and is currently aligning policies and programs to address malnutrition across the country [16]. Results from this study will inform those policies and programs, in both the agriculture and health sectors, on the potential for ASF to be leveraged during pregnancy to improve child health outcomes. By evaluating the effects of maternal egg consumption during pregnancy on child growth outcomes, this study aligns with public health priorities in many LMICs, including Rwanda, where stunting rates remain a health concern. Results from this clinical trial can help shape evidence-based guidelines for prenatal nutrition, potentially influencing government and NGO-led nutrition programs to incorporate affordable, locally available animal-source foods as a strategy to improve maternal and child health outcomes. However, this RCT is limited to a single study site in *Nyagatare* District, Rwanda. Stunting is multi-causal, driven by food intake, gut health, the presence of disease, hygiene, and sanitation, among other determinants [3]. The results of the trial in *Nyagatare* District, Rwanda, may differ from a similar study conducted elsewhere, where stunting may be driven by a different set of determinants. Further studies in different contexts are thus needed, no matter the outcome of this study.

## Trial status

The study protocol (version 1.0) was approved by the Rwanda National Ethics Committee (RNEC) on December 27, 2023, and soon after by the IRB of the University of Florida. The current version of the protocol presented here is version 2.0, which was approved on October 24, 2024. Participant recruitment began on May 02, 2024, with expected completion in September 2025. However, new enrollment is currently on pause due to the termination of USAID funding. The team is actively looking for additional funding, and enrollment will resume as soon as additional funding is secured.

## Data Availability

After the completion of the project, the de-identified data will be deposited into the data repository of the University of Florida and the USAID data repository, where it can be publicly accessed. The dataset in the USAID repository will be findable and identifiable through a study DOI.

## Abbreviations

ANC: Antenatal care
ASF: Animal source foods
BMI: Body mass index
CHW: Community health worker
CREDI: Caregiver-Reported Early Development Instruments
CSB: Corn soy blend
DOI: Digital object identifier
DQQ: Dietary Quality Questionnaire
EPDS: Edinburgh Postnatal Depression Scale
GoR: Government of Rwanda
HNNE: Hammersmith Neonatal Neurological Examination
IEC: Information, education, and communication
IMCI: Integrated management of childhood illness
IOM: Institute of Medicine
IRB: Institutional Review Board
ITT: Intention to treat
LAZ: Length-for-age z-score
LMICs: Low- and middle-income countries
MUAC: Mid-upper arm circumference
RCT: Randomized controlled trial
RNEC: Rwanda National Ethics Committee
SGA: Small for gestational age
USAID: United States Agency for International Development
WHO: World Health Organization
